**2 Protocol summary**

**2.1 Design**

Randomized open label multicentre study.

**2.2 Inclusion**

HIV-1 infected patients naïve to antiretroviral drugs.

No limitations in CD4-cell counts or HIV-RNA levels.

**2.3 Sample size**

Approximately 150-210 patients

**2.4 Treatment regimens**

1. lopinavir/ritonavir (Kaletra®) 400/100 mg BID + 2 NRTIs BID

2. atazanavir (Reyataz ®) 300 mg QD + ritonavir (Norvir®) 100 mg QD + 2 NRTIs QD

3. efavirenz (Stocrin®) 600 mg + QD 2 NRTIs QD

**2.5 Primary trial objective**

1. To determine if there is a difference in the incidence of treatment failure (see 5.5.1 for definition) between the lopinavir/ritonavir BID arm, the atazanavir/ritonavir QD arm, and the efavirenz QD arm.

**2.6 Trial visits**

Pre-entry (earliest 28 days prior treatment initiation) and baseline before therapy start.

On trial evaluations will be completed at week 4 (3-5), 12 (10-14), 24 (22-26), 48 (45-51), 72 (69-75), 96 (93-99), 120 (117-123) and 144 (141-147). In brackets are indicated acceptable deviations from time of follow-up.

On trial evaluation will optionally also be performed at day 7 (6-9), 14 (12-16) and 21 (19-23).

**2.7 Data collection**

A simplified CRF will be filled in and sent by e-mail to the co-ordinating centre following each visit. A copy will be printed out at site and saved in the patient records.

**3 Background and rational**

**3.1 Background and rational**

Antiretroviral combination therapy has markedly decreased the mortality and morbidity in HIV-disease during the last years[1]. The antiretroviral agents presently used are classified in four classes: nucleoside/nucleotide reverse transcriptase inhibitors (NRTIs), non-nucleoside reverse transcriptase inhibitors (NNRTIs), protease inhibitors (PIs), and fusion inhibitors (FIs). An antiretroviral regimen always consists of a combination of drugs, most often three or more from two different classes. An increasing number of new antiretroviral agents have been introduced during the last years and there has been a rapid evolution of new information regarding treatment of HIV. Physicians and patients have to deal with medical associated side effects, problems with adherence, and viral resistance.

The virological goal of the treatment is to suppress and maintain suppression of virological replication, in clinical practice, measured by a decrease in plasma HIV-1 RNA level to below 50 copies/ml. Long-term suppression of HIV-1 RNA levels during antiretroviral treatment depends on good adherence to treatment and achievement of adequate plasma drug levels[2, 3]. In several international studies up to 50% of patients fail treatment with their first antiretroviral combination by the end of one year of therapy. In Scandinavia, higher rates of virological success following antiretroviral therapy have been reported, compared to international studies. Failing therapy is frequently associated with the development of resistance mutations in the HIV genome, often leading to cross-resistance also to other drugs in the same class of antiretrovirals. The chances of a successful treatment are limited if the virus has developed multiple resistance mutations. Consequently, it is important that the first line therapy to the antiretroviral naïve patient is successful. Adherence to the therapy is a major factor to achieve adequate virological efficacy of antiretroviral combination therapy.

To further increase the success rate and effect of treatment, treatment adherence factors such as; treatment regimens with low frequency of side effects, simplified treatment regimens with a low pill burden, few dosing events per day and no food restrictions should be aimed for.

The Swedish guidelines recommend initiation of treatment when the CD4-cell count is in the range between 200 and 350 x 106/l in asymptomatic HIV-infection, and in patients with symptomatic HIV-infection irrespective of the CD4-cell count. As first line therapy, 2 NRTIs in combination with either a NNRTI or a PI is suggested. When PIs are chosen, ritonavir-boosted combinations are most often prefered (PI/r) due to pharmacokinetic and virological reasons[4]. During the last year several drugs have been licensed for dosing once daily (QD), however, only one clinical controlled study between QD and twice-daily (BID) regimens has as yet been published[5]. There are so far no comparable studies between NNRTI-based and PI/r-based regimens given to patients that are antiretroviral naïve published.

The present study aims to compare efficacy, side-effects, and treatment adherence of three different treatment regimens given to antiretroviral naïve HIV-1 infected patients. Treatment will be initiated in accordance with the Swedish National Guidelines. In the BID arm (1), which could be considered as a standard regimen at present, lopinavir/ritonavir, is co-administrated with 2 NRTIs administrated BID. The first QD arm (2) combines the PI atazanavir/ritonavir with 2 NRTIs administrated QD, and in the second QD arm (3), the NNRTI efavirenz is combined with 2 NRTIs administrated QD. All drugs used in the study are licensed in the participating countries and patients will be followed as in clinical practice. Patients could optionally, after informed consent, be followed with additional measurements of HIV-1 RNA after 1, 2, and 3 weeks of treatment to asses the kinetics of viral decline after initiation of treatment.

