**5.2 Secondary objectives**

1. To clarify whether there are any differences in adherence to treatment between the three arms.

2. To address whether there is a difference between the arms in the incidence of side-effects, including hyperlipidemia, leading to regimen discontinuations or changes.

3. To evaluate differences between the arms in the kinetic of viral suppression during the first four weeks of treatment (optional).

4. To explore the reason for premature discontinuing of randomised treatment.

5. To determine differences in the CD4-cell count response

6. To assess the safety and tolerance of the three treatment arms

7. To assess changes in genotypic resistance in plasma HIV-1 over the study period in the different arms

8. To determine the plasma concentration of the PIs and NNRTIs in steady state, i.e. 2-4 weeks after starting study medication

9. To assess changes in laboratory parameters, plasma lipids included, over the study period

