**5.4 Secondary endpoints**

1. Estimated adherence rate

2. Proportion of treatment discontinuations and changes due to different adverse events.

3. Decrease in HIV-1 RNA during the first 4 weeks of treatment (optional)

4. Proportion of patients with plasma HIV-1 RNA levels below 50 copies/ml after 4, 12, 24, 48, 72, 96, 120 and 144 weeks of treatment. Both Intention to Treat (ITT) and On Treatment (OT) analyses will be performed.

5. Changes in CD4+ T-cell count from baseline.

6. Time to discontinuation or changes of randomised treatment and reasons for this.

7. Incidence of adverse events.

8. Incidence of genotypic resistance to NRTIs, NNRTIs, and PIs that develops during the study

9. Proportion of patients with adjusted drug doses after therapeutic drug monitoring.

10. Correlations between plasma drug concentrations and virological outcome and adverse events.

11. Changes from baseline in plasma lipids.

12. Incidence of hypercholesterolemia and hypertriglyceridemia at baseline and follow-up.

13. Incidence of abnormal laboratory parameters (Hb, LPK, ASAT, ALAT, ALP, Bilirubin, S-amylas, Creatinin)

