***7.1.2 Randomisation***

Patients eligible to the study and who have signed informed consent may be randomised as soon as results from viral load and CD4 cell count measurements are available.

The randomisation (1:1:1) is performed at the Department of Infectious Diseases, Sahlgrenska University Hospital/Östra and is stratified for CD4-cell count (< or ≥ 200 x 106/ml) and plasma HIV-1 RNA level (< or ≥ 100 000 copies/ml).

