**7.2 On trial evaluations**

On trial evaluations will be completed at week 4 (3-5), 12 (10-14), 24 (22-26), 48 (45-51), 72 (69-75), 96 (93-99), 120 (117-123) and 144 (141-147). In brackets are indicated acceptable deviations from time of follow-up.

In-between visits according to local praxis, and laboratory tests other than those settled in the study protocol, will be conducted outside the study.

The following evaluations will be performed at each visit if nothing else is stated:

 Current antiretroviral therapy including eventual dose modifications, interruptions, or discontinuations.

 Adherence to treatment

 New HIV-associated complications.

 Side-effects and laboratory pathology

 Weight (week 4, 48, 96, and 144)

 CD4-cell count

 Quantitative plasma viral load (HIV-1 RNA)

 Blood lipids, i.e. total cholesterol, LDL, HDL, triglycerids (fasting)

 Hb, LPK, ASAT, ALAT, ALP, Bilirubin, S-amylas, Creatinin, fB-glukos

 Plasma concentration of NNRTI and PI 12-24 hours after last drug intake (at week 4, 48, 96 and 144)

 2 x 10 ml plasma for storage in –70oC at study site

On trial evaluations will optionally also be performed at day 7 (6-8), 14 (12-16) and 21 (19-23) including:

 Current antiretroviral therapy including eventual dose modifications, interruptions, or discontinuations

 Adherence to treatment

 New HIV-associated complications.

 Side-effects and laboratory pathology

 Quantitative plasma viral load (HIV-1 RNA)

 Hb, LPK, ASAT, ALAT, ALP, Bilirubin, S-amylas, Creatinin, fB-glukos (at day 14)

 2 x 10 ml plasma for storage in –70oC at study site

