**Table 1**

Clinical and laboratory evaluations at pre-entry and baseline

| **Evaluation** | **Screening&baseline** |  |
| --- | --- | --- |
|  | **d. -28 - 0** | **d. 0** |
| Informed consent | X |  |
| Entry criteria and demography | X | (X)f |
| Randomisation |  | Xi |
| CDC Classification | X | (X)f |
| Medicationsa | X | X |
| Adherence estimation |  |  |
| HIV-associated conditionsb | X | X |
| Plasma HIV-1 RNA quantitative PCRc | Xj | X |
| CD4 cell count | X |  |
| Blood lipids (Total Cholesterol, LDL, HDL, TG) (fasting) | X | (X)f |
| Hb, LPK, ASAT, ALAT, ALP, Bilirubin, S-amylas, Creatinin, fB-glukos | X | (X)f |
| Plasma ~~concentration of NNRTI and PI~~~~d~~  ~~and~~ 4bOHcd |  | X |
| Plasma sample collectione | X | X |
| Hepatits serology (HBsAg, anti-HCV)h | (X) |  |
| Weight | X | (X)f |

a Antiretroviral therapy including dose modifications, interruptions, discontinuations, and reasons for change should be indicated. All other drugs that are taken regularly should be indicated.

b At baseline, also the history of previous HIV-associated conditions.

c The HIV-1 RNA determination is done real-time at the site using routine virological methodology at that site, preferably the Roche Amplicor Ultrasensitive assay. The same method should be used for the individual subject throughout the trial.

d ~~12-24 hours after the last dose,~~ 10 ml heparin tube, centrifuged, plasma sent to Clin. Pharm., KU Huddinge (label: NORTHiv 4bOHc)

e 2 x 10 ml or 3 x 6 ml EDTA tubes, plasma collected and stored in –70oC at study site.

f if not performed on the previous visit

g ~~not necessary if HIV-1 RNA from screening visit performed within 2 weeks from baseline~~

h if not performed earlier

i randomisation could be performed before day 0 provided informed consent is signed and results from viral load and CD4 cell count are available

**j** HIV-1 RNA PCR obtained in clinical practice before initiation might be used for screening as long as it was obtained within the time limit (≤28 days before treatment initiation at baseline)

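### The day 7, 14 and 21 comparison of viral kinetics between arms is not guaranteed a randomised basis, because patients may opt in after their arm is known

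*Protocol*

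**What the plan says.** Section 2.1 describes the trial as follows: "Randomized open label multicentre study". Secondary objective 3 (section 5.2) is worded as a comparison of arms: "To evaluate differences between the arms in the kinetic of viral suppression during the first four weeks of treatment (optional". The matching endpoint in section 5.4 is "Decrease in HIV-1 RNA during the first 4 weeks of treatment (optional".

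The samples that would describe the first three weeks are voluntary. Section 3.1 states: "Patients could optionally, after informed consent, be followed with additional measurements of HIV-1 RNA", at weeks 1, 2 and 3. Section 7.2 repeats this: "On trial evaluations will optionally also be performed at day 7 (6-8), 14 (12-16) and 21 (19-23) including". Table 2 marks each of the three visits as optional in its own column, so a patient may attend one and skip another.

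On the order of events, section 7.1.2 says "Patients eligible to the study and who have signed informed consent may be randomised as soon as results from viral load" and CD4 count are available. Footnote i of Table 1 adds that "randomisation could be performed before day 0 provided informed consent is signed" and those results are at hand. Trial consent therefore comes before randomisation, and randomisation may come before treatment starts. No section says when the choice about the optional visits is made or recorded.

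HIV-1 RNA at baseline (section 7.1.1) and at week 4 (section 7.2, Table 2) is scheduled for every patient. Section 9 names Kruskal-Wallis for continuous variables.

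**The concern.** Randomisation makes the arms comparable as randomised. It also makes a subset comparable if membership was settled before allocation or does not depend on it. A subset that can form once the arm is known has no such protection.

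Uptake could differ by arm for several reasons: a clinician's interest in one regimen, a patient's expectations of it, or side effects in the first days. If the reasons for taking part are related to early HIV-1 RNA decline, for example through baseline viral load, a difference in kinetics could reflect who volunteered. The protocol stratifies randomisation on HIV-1 RNA at 100 000 copies/ml, but that balance need not carry over to volunteers. Kruskal-Wallis as named in section 9 makes no adjustment for baseline.

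What is at stake is the interpretation of the week 1 to 3 data, which are the sole purpose of the extra visits. If the choice was made after allocation and its timing not recorded, no later analysis can restore the comparison.

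**Working it through.** **Plan's own figure.** None is given for the kinetics comparison. The power statement in section 9 (65 per group, success 0.70 against just over 0.90) concerns treatment failure and plays no part here.

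**Order of events.**
1. Consent to the trial, before randomisation (section 7.1.2).
2. Randomisation, on or before day 0 (Table 1, footnote i). With no blinding, the arm can be known from here on.
3. Treatment starts on day 0.
4. Optional visits on days 7, 14 and 21.
5. Week-4 visit, scheduled for all.

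The only stated condition on the extra sampling is that consent has been given. Any moment after step 1 satisfies it, including the whole interval from step 2 to step 4. Opt-in with the arm known is thus allowed. Opt-in at step 1 is allowed too.

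**Which data are exposed.** Days 7, 14 and 21 only. Baseline and week-4 values are scheduled for everyone, so the change from baseline to week 4 can be compared in all randomised patients.

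**Illustration of size.** All inputs are assumptions, and none comes from the protocol. There is no true arm difference. A trait present in half of patients raises the log10 fall by 0.3. The SD of the fall is 0.5. There are 33 volunteers per arm, and two arms are compared by a two-sided z-test at 0.05.

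- Share of volunteers with the trait = 0.5·p₁ / (0.5·p₁ + 0.5·p₀), where p₁ and p₀ are the opt-in rates with and without the trait.
- Bias = 0.3 × (share in arm A − share in arm B).
- SE = 0.5 × √(2/33) = 0.123.
- Type I error = 1 − Φ(1.96 − bias/SE) + Φ(−1.96 − bias/SE).

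| Opt-in, arm A (p₁/p₀) | Opt-in, arm B (p₁/p₀) | Share A − share B | Bias (log10) | Type I error |
|---|---|---|---|---|
| 60%/40% | 60%/40% | 0 | 0 | 5.0% |
| 60%/40% | 50%/50% | 0.1 | 0.03 | 5.7% |
| 70%/30% | 50%/50% | 0.2 | 0.06 | 7.8% |
| 70%/30% | 40%/60% | 0.3 | 0.09 | 11.3% |

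In the first row volunteers are selected, but in the same way in both arms, and there is no bias. The harm comes from selection that differs by arm. A choice fixed before allocation cannot differ by arm except by chance.

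**The case against.** A reader might infer that this comparison has lost its randomised basis, or that the protocol as written yields a non-randomised comparison. The text does not support that. Nothing in it places opt-in after allocation. The only consent step it describes comes before randomisation, and one natural reading is that the extra sampling is agreed then. The consent form was not available for this review and may already carry a yes/no choice. If it does, or if uptake is unrelated to arm, the comparison among those who opted in stays randomised. All of this stands, and it limits the point to what the protocol permits.

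It is also fair that the objective is secondary and marked optional, that only the day 7 to 21 data are exposed, and that the illustration rests on invented inputs. Its largest figure needs uptake to run in opposite directions in the two arms. Imbalance in baseline HIV-1 RNA could be seen and adjusted for, since everyone is measured. Imbalance in unmeasured reasons for volunteering could not.

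A further objection is that a choice recorded before randomisation does not stop patients from skipping days 14 and 21 because of early side effects. That is correct. It is why the comparison should include everyone who said yes, with attendance reported by arm.

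The argument that the analysis plan will deal with it does not stand for the timing of opt-in, which is a matter of trial conduct. The choice of analysis set and of baseline adjustment could be made there.

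**Conclusion.** The point holds in limited form. In an open-label trial, a between-arm objective draws on visits that patients may choose after learning their arm, so the day 7 to 21 comparison is not guaranteed a randomised basis. Whether selection by arm would occur, in which direction and how strongly, cannot be derived from the protocol. The 0 to 0.09 log10 and 5.0% to 11.3% above are illustrations on assumed inputs and not estimates for this trial. The primary endpoint is untouched, and so is a week-4 comparison made in all randomised patients. This is a minor point, worth acting on because the remedy is cheap beforehand and unavailable afterwards.

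**What to change.** 1. In section 7.2, require the yes/no choice for the day 7, 14 and 21 visits to be recorded before randomisation. If the consent form already does this, say so there. Compare arms among all who said yes at that point, whether or not they attend every visit. Report opt-in numbers, attendance and baseline data by arm.
2. In sections 5.4 and 9, make the change in HIV-1 RNA from baseline to week 4 in all randomised patients, adjusted for baseline HIV-1 RNA, the main between-arm comparison for endpoint 3. Remove the optional label from that part and treat the day 7 to 21 data as supportive.

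The cost is one tick-box on the consent form or CRF and a few sentences. No visit or sample is added. The small downside is that patients who volunteer after allocation are left out of the day 7 to 21 comparison, though their data can still be described.

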**3.2 Study drugs**

Lopinavir and efavirenz are approved for first-line treatment of HIV-1 infection. Atazanavir is approved by FDA in USA. In Europe it is available for prescription through licence and assumed to be approved soon. Details of the studied drugs can be found in the product labelling information released by the manufactures.

**3.3 Dosage of study drugs**

Lopinavir is nearly completely metabolised through the hepatic cytochrome P450 system via the CYP3A4 isoform. Lopinavir is, however, co-formulated with a low dose ritonavir (100 mg) which is a potent inhibitor of CYP3A4 and substantially enhances the exposure of lopinavir. The approved dose of lopinavir/ritonavir, 400/100 BID, is used in the study[6]. NNRTIs could induce CYP3A4 and it is recommended to increase the lopinavir/ritonavir dosage to 533/133 mg BID when co-administrated with NNRTIs. Lopinavir/ritonavir is not used together with NNRTIs in this study.

The approved dose of atazanavir is 400 mg QD[7]. Similar to lopinavir, atazanavir is metabolized through CYP3A4 and when co-administrated with ritonavir (100 mg QD), the dosage is normally reduced to 300 mg QD[8]. Tenofovir, a NRTI often used in QD regimens, reduce atazanavir (unboosted) AUC with 25 % and Cmin with 40 % (BMS study AI454-181, unpublished results). When co-administrated with ritonavir-boosted atazanavir (300 mg + 100 mg ritonavir QD), tenofovir reduce AUC with 25 % but due to higher exposure, adequate Cmin (513 ng/ml) is preserved[9]. The Swedish Recommendations favour ritonavir-boosting when PIs are used[4] and by pharmacokinetic and virological reasons atazanavir/ritonavir 300/100 mg QD has been chosen as dosage in this study.

Efavirenz is approved for dosage of 600 mg QD. Therapeutic drug monitoring for dose adjustment is an option and efavirenz plasma levels seems to correlate with virological outcome and central nervous system side effects[10, 11].

**3.4 Interactions with other drugs**

A lot of drug interactions are present between several drugs and the study drugs. The risk of interactions should be carefully considered when other medications will be given concomitant. Since drug interactions with ritonavir-boosted atazanavir are not sufficiently studied, a particular cautious has to be taken with this drug. It should be noted that drugs that decrease the gastric acid, such as H2-antagonists and proton pump inhibitors may substantially reduce the absorption of atazanavir and should thus be avoided.

**4 Treatment regimens**

**4.1 Randomised treatment arms**

Patients will be randomized to one of three study arms (1:1:1). Randomization will be stratified according to CD4-cell count (above or below 200 x 106/l) and plasma HIV-RNA level (above or below 100 000 copies/ml).

Study arms:

1. lopinavir/ritonavir (Kaletra®) 400/100 mg BID + 2 NRTIs BID

2. atazanavir (Reyataz ®) 300 mg QD + ritonavir (Norvir®) 100 mg QD + 2 NRTIs QD

3. efavirenz (Stocrin®) 600 mg QD + 2 NRTIs QD

**4.2 Therapeutic drug monitoring**

Plasma concentrations of lopinavir, atazanavir and efavirenz will be analyzed after 4 weeks of treatment.

The dose of efavirenz may be adjusted after therapeutic drug monitoring in accordance with clinical practice.

**5 Study objectives**

**5.1 Primary objectives**

1. To determine if there is a difference in the incidence of treatment failure (see 5.5.1 for definition) between the lopinavir/ritonavir BID arm, the atazanavir/ritonavir QD arm, and the efavirenz QD arm.

**5.2 Secondary objectives**

1. To clarify whether there are any differences in adherence to treatment between the three arms.

2. To address whether there is a difference between the arms in the incidence of side-effects, including hyperlipidemia, leading to regimen discontinuations or changes.

3. To evaluate differences between the arms in the kinetic of viral suppression during the first four weeks of treatment (optional).

4. To explore the reason for premature discontinuing of randomised treatment.

5. To determine differences in the CD4-cell count response

6. To assess the safety and tolerance of the three treatment arms

7. To assess changes in genotypic resistance in plasma HIV-1 over the study period in the different arms

8. To determine the plasma concentration of the PIs and NNRTIs in steady state, i.e. 2-4 weeks after starting study medication

9. To assess changes in laboratory parameters, plasma lipids included, over the study period

